## Abstract

**Background::**

Rheumatic diseases affect approximately 54 million adults in the United States and are a leading cause of pain and disability. Although physical activity is recommended to reduce pain and improve function, rheumatic diseases encompass over 100 conditions with different clinical presentations and medical management, possibly contributing to differences in exercise response. Few studies have included diverse samples across rheumatic diseases making direct comparisons in clinical presentation and activity level difficult.

**Objective::**

To evaluate the feasibility of internet recruitment, validate patient-reported diagnoses, and explore associations of physical activity with pain and function across rheumatic diseases in an online cohort of adults in the United States.

**Methods::**

The Observational Arthritis foundation Internet Study (OASIS): Physical Activity, Pain, and Physical Function study is an online cross-sectional observational study of adults with rheumatic diseases living in the US. Participants will be recruited using Meta ads, Arthritis Foundation mailing lists, and the ResearchMatch database. Participants will be considered eligible if they are ≥ 18 years old, live in the US, and have been diagnosed with a rheumatic disease by a physician. All participants will provide written informed consent and HIPAA release prior to participation. Participants will self-report all rheumatic diseases they have been diagnosed with, and diagnoses will be verified using provider confirmation or electronic medical records. Self-report questionnaires will be used to assess outcomes such as physical activity, pain, physical function, mental and physical health.

**Discussion::**

OASIS is the first study to comparison of physical activity, pain, and physical function across a range of rheumatic diseases in a single cohort. The results from this study could identify differences in presentation or inform tailored exercise recommendations for less common rheumatic diseases.

## Introduction

One in five adults in the United States report being diagnosed with a rheumatic disease,^1,2^ accounting for more than $300 billion in direct medical costs and lost wages in 2013.^3^ Rheumatic diseases, a term which encompasses over 100 conditions including osteoarthritis (OA), rheumatoid arthritis (RA), and lupus, are a leading cause of pain and functional limitations.^1,4–7^ These symptoms interfere with performing daily activities, reduce quality of life, and lead to decreased physical activity.^1,2,8–10^ Reduced physical activity in turn increases risk of other comorbidities such as obesity, cardiovascular disease, and early mortality.^11,12^

Exercise and physical activity are strongly recommended treatments for adults with rheumatic diseases especially OA^13,14^ and RA,^15,16^ two of the most prevalent. Additionally, increased physical activity is associated with reduced risk of mortality, improved muscle strength, and improved psychological health in both the general population^11,12,17,18^ and adults with OA^13,19–21^ and RA.^15,22–25^ Previous research has also shown that increasing physical activity improves pain and function in adults with OA^13,19–21^ and RA.^15,22–25^ Despite these benefits, there is little research examining the effects of physical activity in other types of rheumatic diseases such as lupus, psoriatic arthritis, and gout.

Observational studies are well-suited to study such differences in treatment response and clinical presentation across rheumatic diseases. However, most studies focus on adults with OA or RA, limiting the ability to compare across other rheumatic diseases and to make evidence-based recommendations for less common diseases. Therefore, additional comparisons are needed to understand how physical activity relates to pain and function in adults with different forms of rheumatic disease. This paper outlines the protocol for the Observational Arthritis Foundation Internet Study: Physical Activity, Pain, and Function (OASIS). OASIS aims to evaluate the feasibility of internet recruitment, validate patient-reported diagnoses, and explore associations of physical activity with pain and function across rheumatic diseases.

## Methods

### Study Design

The Observational Arthritis foundation Internet Study (OASIS): Physical Activity, Pain, and Physical Function study is a completely online cross-sectional observational study focusing on adults with different forms of rheumatic disease, such as osteoarthritis (OA), gout, lupus, fibromyalgia, rheumatoid arthritis (RA), and psoriatic arthritis (PsA). This study will measure physical activity, pain, and physical function on adults with rheumatic diseases living in the United States. Study findings will be reported using the STROBE guidelines for observational studies.

### Participants

Individuals will be recruited using Meta advertisements primarily through Facebook, the Arthritis Foundation mailing list, and via the ResearchMatch participant database. ResearchMatch is a national health volunteer registry that was created by several academic institutions and supported by the U.S. National Institutes of Health as part of the Clinical Translational Science Award (CTSA) program. ResearchMatch includes volunteers who have consented to be contacted by researchers about health studies for which they may be eligible. Review and approval for this study and all procedures was obtained from University of Delaware Institutional Review Board. Participants will be included if they are at least 18 years old, live in the United States, and report having a diagnosis of a rheumatic disease provided by a physician. Participants self-report diagnoses of OA, gout, fibromyalgia, RA, psoriatic arthritis (PsA), lupus, or ‘other’ rheumatic disease. Additionally, participants must have internet access, a working email address, feel comfortable answering questions in English, and be willing to have a virtual call to verify their identity. Participants will be excluded if they fail to meet any of the inclusion criteria, have been previously enrolled, or fail the identity verification check.

### Identity Verification Check

We will employ a multi-step strategy to identify individuals who purposefully falsify information to secure payment for participation. We will utilize these strategies to check the validity of reporting from study participants during the enrollment phase. The Internet Protocol (IP) address used by the participant will be analyzed using website-based software to determine if it is located within the United States and does not have evidence of fraud or abuse. Then the informed consent form will be analyzed to ensure the printed name and signed name are consistent and match the name and signature provided on the HIPAA authorization form, if there are inconsistencies in the names, not including addition of middle initials or full versions of first name, the participant will be deemed fraudulent and excluded from the study. Additionally, if the name on the HIPAA form is not the participant’s name and/or the relationship to the participant is something other than self or equivalent (ex., Doctor, friend), then the participant will be excluded from the study. Lastly, we will examine answers to the screening form to ensure that the name provided matches the informed consent and HIPAA forms. If the participant passes all these criteria, they have passed the identity verification check and will be enrolled in the study.

### Enrollment and data collection

Participants who meet study criteria, sign the informed consent and HIPAA authorization forms, and pass the identity verification check will be enrolled. Participant demographics will then be collected, including age, sex, gender, body mass index (BMI), race, whether they were Latino, veteran status, highest level of education, employment status, and annual household income. Self-reported data on their reported rheumatic disease, physical activity, and other outcomes will also be collected.

### Disease Specific Information

Participants will self-report which rheumatic diseases they have been diagnosed with by a physician and the date of diagnosis for each. Participants will select from a list of OA, gout, fibromyalgia, RA, PsA, Lupus, or Other. If other is selected, participants are able to write in any other rheumatic disease they are diagnosed with. Participants will also be able to select multiple diagnoses. If the participant reports being diagnosed with osteoarthritis, they will be asked to report which joints were affected. National Institute for Health and Care Excellence (NICE) criteria for knee OA (≥ 45 years old, activity-related knee pain, and morning stiffness lasting < 30 minutes)^26^ will be assessed in all participants who report OA and specified the knee joint being affected. NICE Criteria have been shown to be sensitive and specific in detecting symptomatic knee OA. Participants will also be asked about previous joint injuries, joint surgeries, and past and current strategies used to manage their disease related symptoms, including options such as physical therapy, diet, corticosteroid injections, immunosuppressants, nonsteroidal anti-inflammatory medications, etc. The use of glucagon-like peptide-1 (GLP-1) agonists will also be assessed.^27,28^

## Primary Outcomes

### Physical Activity

Physical activity will be assessed using the International Physical Activity Questionnaire – Short Form (IPAQ-SF). The IPAQ-SF is a seven-item questionnaire that assesses self-reported physical activity in categories of vigorous activity, moderate activity, walking, and sedentary behavior in the form of sitting.^29–31^ Participants are asked to report the total number of minutes per day and days per week that they engage in vigorous, moderate, and walking activities. The total number of metabolic equivalent units (MET)- minutes in each category is then calculated by multiplying the total number of minutes and days in each category by the MET value for each category (8.0 MET for vigorous, 4.0 for moderate, 3.3 for walking).^32^ Participants are also classified as inactive, minimally active, and health-enhancing physical activity (HEPA) active based on the total combined MET-minutes/week calculations.^32^ HEPA active category is defined as vigorous activity on at least three days and achieving at least 1500 MET-min/wk or 7 or more days of any activity to achieve at least 3000 MET-min/wk.^32^ Minimally active is defined as 3 or more days of vigorous activity for at least 20 min/day, 5 or more days of moderate or walking activity of at least 30 minutes/day, or 5 or more days of any combination of activity achieving at least 600 MET-min/wk.^32^ Inactive is defined as reporting no activity or activity insufficient to meet the criteria for the other two categories.^32^ Sedentary behavior is assessed with one question asking participants to report the total time sitting on an average weekday.^32^ The scoring guidelines for the IPAQ-SF will be utilized for data processing, including handling outliers, truncation of data, and minimal values for activity duration.

### Pain

The primary measure that will be used to assess pain is the Patient-Reported Outcomes Measurement Information System Pain Interference Short Form 8a (PROMIS-PI 8a). The PROMIS-PI is an 8-item questionnaire that assesses self-reported pain interference that has been validated in healthy adults and multiple clinical populations.^33–35^ Additional measures of pain will include the Visual Analog Scale (VAS) for pain and the Michigan Body Map (MBM) for chronic pain. The VAS will be collected from participants who reported a diagnosis of knee OA. This single-item questionnaire asks the participants to make a mark on a 100 mm line to indicate their pain score from 0–100 where zero represents no pain and 100 represents the worst pain imaginable.^36^ The MBM will be collected from all participants, who reported chronic pain, which is pain that is persistent or recurring pain lasting for three months or longer at the time they completed the questionnaire. Participants were asked to select on a human body map all regions where they were experiencing chronic pain. This measure has been validated in adults and is commonly used during the diagnosis of fibromyalgia.^37,38^

### Physical Function

Self-reported physical function will be measured using the Patient-Reported Outcomes Measurement Information System Physical Function Short Form 6b (PROMIS-PF 6b). The PROMIS-PF is a 6-item questionnaire that assesses self-report difficulty performing daily activities such as walking and household chores. This questionnaire has been validated in both healthy and clinical populations.^34,39–41^

## Secondary Outcomes

### Health Status

Overall health status will be measured using the PROMIS Global Health (PROMIS-GH) questionnaire. This 10-item questionnaire assesses overall health and quality of life including subscale scores for mental and physical health. Participants will also complete the Charlson Comorbidity Index (CCI) questionnaire. The CCI is a 17-item questionnaire that creates a weighted score based on a range of comorbidity conditions.

### Kinesiophobia

Kinesiophobia will be assessed using the Tampa Scale of Kinesiophobia (TSK-11). This abbreviated version of the TSK is an 11-item questionnaire that evaluates an individual’s fear-avoidance of movement, fear of work-related activities, and fear of re-injury. This questionnaire has been validated among adults with chronic pain.^42^

### Diagnosis Verification

Self-reported diagnoses will be verified via physician report or electronic medical record (EMR). Participants will specify whether they will provide EMR verification of their diagnoses or if they would prefer the research team to contact their physician for verification. Participants will then either upload a screenshot or scanned document from his/her EMR where their diagnosis is specified, or their physician will complete a provided diagnosis form template. In any instances where the specified diagnosis is unclear, the research team will adjudicate to determine whether the diagnosis can be confirmed.

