## Analysis plan

We will use descriptive statistics, mean and standard deviation for continuous variables and frequency and percent for categorical variables, to summarize participant characteristics and study outcomes. To determine feasibility of recruitment, we will calculate the time to recruit 1500 participants and the cost per study completer. We will calculate percent agreement and kappa coefficients with associated 95% confidence interval to determine validity of self-reported diagnoses. We will estimate the cross-sectional association of physical activity, pain, and physical function using linear regression adjusted for potential confounders.

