### Strengths

OASIS utilizes a novel completely online recruitment strategy. This allows for recruitment of a geographically diverse sample and inclusion of individuals from rural areas, which are typically understudied. Additionally, this is the first study to include individuals with all rheumatic diseases, allowing for comparisons across rheumatic diagnoses which were not previously possible. The use of validated outcome measures strengthens the reliability of the data, and inclusion of physician verification of diagnoses increases accuracy of rheumatic disease classification.

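### On the EMR route participants choose the page that is to verify their own diagnosis, so this route confirms more readily than it refutes, and agreement among returned uploads is liable to be too high

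*Protocol article*

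**What the plan says.** The Protocol article (Abstract, Objective; Introduction) names validation of patient-reported diagnoses as one of three aims. Diagnosis Verification sets out how it is done:

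- The participant picks the route: "Participants will specify whether they will provide EMR verification of their diagnoses or if they would prefer the research team to contact their physician".
- On the record route: "Participants will then either upload a screenshot or scanned document from his/her EMR where their diagnosis is specified".
- On the other route: "or their physician will complete a provided diagnosis form template".
- For doubtful evidence: "In any instances where the specified diagnosis is unclear, the research team will adjudicate to determine whether the diagnosis can be confirmed".

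The Analysis plan then states: "We will calculate percent agreement and kappa coefficients with associated 95% confidence interval to determine validity of self-reported diagnoses". It gives no expected value. It does not say how a diagnosis without returned evidence is counted, or whether the two routes are combined. Among the study's strengths the article lists: "inclusion of physician verification of diagnoses increases accuracy of rheumatic disease classification".

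**The concern.** A validation study needs evidence that can come out either way. On the EMR route the evidence is chosen by the person under test, and what is requested is a page on which the diagnosis stands. Someone whose record does not carry the reported diagnosis will often have no such page, so the error surfaces as a non-return. If returned uploads form the denominator, those errors drop out of the agreement figure.

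No complete problem or diagnosis list is requested. A rheumatic disease that is in the record but was not reported will therefore seldom be seen, and kappa has little sound information on the negatives.

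False reports are a risk that the article itself foresees. Its section Identity Verification Check anticipates people who falsify information to obtain payment. The checks described there concern the IP address and the consistency of names, and none tests the diagnosis. Diagnosis verification is the step that could detect a false diagnosis, and its record route is the less able of the two to do so. At stake is the validity estimate, and the trust placed in the disease groups that the study sets out to compare.

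**Working it through.** The article states no agreement, kappa or precision figure, so there is nothing to reproduce. Every input below is an assumption, except the 1500 participants, which is the recruitment target in the Analysis plan.

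**Inputs.** p = share of self-reports that are true. u = probability that a true reporter returns evidence. c = probability that a false reporter returns contradicting evidence. s = share choosing the EMR route. r = response on the physician form, taken as accurate and unrelated to whether the report is true.

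**EMR route, returned uploads only.** Agreement = p·u / [p·u + (1 − p)·c]. With p = 0.7 and u = 0.8:

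| c | Calculation | Agreement |
|---|---|---|
| 0.1 | 0.56 / (0.56 + 0.03) | 95% |
| 0.2 | 0.56 / (0.56 + 0.06) | 90% |
| 0.5 | 0.56 / (0.56 + 0.15) | 79% |
| 0.8 | 0.56 / (0.56 + 0.24) | 70% |

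The last row has no selection (c = u) and gives back the assumed truth.

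**Where the errors go.** Take 100 reports with c = 0.1. Then 56 are confirmed, 3 are refuted and 41 are not returned. The 41 are 14 true reports (0.7 × 0.2) and 27 false ones (0.3 × 0.9). So 27 of the 30 false reports never reach the comparison.

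**Other values of p.** With u = 0.8 and c = 0.05, agreement among returns is 96.0%, 97.4% and 99.3% for true accuracy of 60%, 70% and 90%. With c = 0.2 it is 85.7%, 90.3% and 97.3%.

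**EMR route, every non-return counted as unconfirmed.** Confirmed share = p·u = 0.7 × 0.8 = 56%, which is below the assumed truth of 70%.

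**Both routes combined, returned evidence only.** Agreement = [s·p·u + (1 − s)·r·p] / [s·(p·u + (1 − p)·c) + (1 − s)·r]. With s = 0.5, r = 0.6, c = 0.1: (0.28 + 0.21) / (0.295 + 0.30) = 0.49 / 0.595 = 82%.

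**Kappa.** If only reported diagnoses are checked, the table has no negatives. Kappa is then 0 whether 70% or 97% are confirmed, and undefined at 100%. Now take a full table for one disease, with 1500 participants and 300 self-reports:

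- 70% confirmed, and 60 of the 1200 non-reporters in fact have the disease: observed agreement 0.900, chance agreement 0.692, kappa = 0.208 / 0.308 = 0.68.
- 70% confirmed, and those 60 go unseen and count as absent: 0.940 and 0.716, kappa = 0.224 / 0.284 = 0.79.
- 97.4% confirmed (the c = 0.05 case for a truth of 70%), and the 60 unseen: kappa = 0.98.

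**The case against.** Several stronger readings are tempting, and the text does not carry them.

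- **Agreement near 100% by construction.** This needs non-returns to be left out, nearly everyone to choose the EMR route, and contradicting uploads to be very rare. The article fixes none of these. The physician form can return a no. A participant who is wrong about the type of disease has a page to upload, and that page refutes the report. Nothing forbids uploading more than one page.
- **Bias in one direction only.** The direction depends on the denominator. If non-returns count as unconfirmed, the same inputs give 56% against a truth of 70%.
- **The two routes are pooled.** The Analysis plan does not say so.
- **Adjudication leans towards agreement.** Asking whether a diagnosis "can be confirmed" also allows the answer that it cannot, and the article does not say what the adjudicators see.
- **The study will recommend self-report to others.** The Implications section speaks only of informing methods for internet-based recruitment.

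It is also fair to say that a condensed article may leave the counting rule and reporting by route to a fuller document, so their absence here is not a fault. What stands is the collection rule itself. The participant's choice of route and the kind of page requested are stated in the article, and no later analysis can recover pages that were never asked for.

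**Conclusion.** The point holds in a limited form. The EMR route confirms a self-report more readily than it refutes one and seldom reveals unreported diagnoses, so agreement among returned uploads is liable to be too high. The amount is unknown. Under the assumed 70% truth and 80% return by true reporters, the EMR figure among returns runs from 79% to 95% as c falls from 0.5 to 0.1. A half share of physician forms at 60% response brings the 95% down to about 82%. The strict EMR count is 56%. These figures show sensitivity to unstated quantities and are not forecasts. The upward direction applies to returned evidence and rests on false reporters returning evidence less often than true ones (c < u).

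The wording in Strengths is a lesser matter. The article names both routes openly, but the phrase on physician verification does not describe the participant-supplied documents.

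**What to change.** 1. Ask EMR-route participants to upload their full problem or diagnosis list instead of a page showing the reported diagnosis.
2. Over all self-reported diagnoses, report the numbers confirmed, refuted, unclear and not returned. Give the confirmed share as a range: returned evidence only, and non-returned or unclear counted as unconfirmed. State that the returned-only figure is an upper limit only if c does not exceed u.
3. Show percent agreement and kappa for the EMR and physician-form routes side by side. Treat neither as unbiased, because participants choose the route and the physician form has non-response of its own.
4. Have unclear documents classified by disease without sight of the self-report.
5. Word the strength as verification by physician form or participant-supplied record.

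Items 2 to 4 need only wording if a fuller plan does not already contain them, plus the masking of one field for the adjudicators. Item 1 is a slightly larger request to participants. The price is a lower and wider agreement figure.

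### Unclear diagnosis records are adjudicated by asking whether the diagnosis can be confirmed, with no stated masking to the self-report, so agreement may be inflated among those records

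*Protocol article*

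**What the plan says.** Checking self-reported diagnoses is one of the study's three objectives; the abstract's Objective lists it as "validate patient-reported diagnoses".

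The Diagnosis Verification section (under Secondary Outcomes) describes the reference:

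- Its opening sentence sets the subject: "Self-reported diagnoses will be verified via physician report or electronic medical record (EMR").
- The participant picks the route: "Participants will specify whether they will provide EMR verification of their diagnoses or if they would prefer the research team to contact their physician".
- On the record route, "Participants will then either upload a screenshot or scanned document from his/her EMR where their diagnosis is specified". On the other route the physician fills in a form supplied by the study.
- For ambiguous material on either route: "In any instances where the specified diagnosis is unclear, the research team will adjudicate to determine whether the diagnosis can be confirmed".

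The Analysis plan then says: "We will calculate percent agreement and kappa coefficients with associated 95% confidence interval to determine validity of self-reported diagnoses".

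The article does not say whether adjudicators see the self-reported diagnosis. It gives no figure for expected agreement, kappa, or the share of records that will be unclear.

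**The concern.** Percent agreement and kappa measure validity only if the reference is read independently of the report being tested. The adjudication question is framed as whether a diagnosis can be confirmed. A yes-or-no question of that kind starts from a candidate diagnosis. When the record is unclear, the record cannot readily supply the candidate, so the participant's report is the natural source. A neutral question would ask which disease the record documents.

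If adjudicators work from the claim, the same vague entry could be accepted as osteoarthritis for one participant and as rheumatoid arthritis for another. The self-report would then help to create the standard against which it is judged (review or incorporation bias). The 95% confidence interval reflects sampling error only and would not reveal this. At stake is how far the reported agreement can be trusted as a measure of self-report validity, and with it the article's claim under Strengths that verification makes disease classification more accurate.

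**Working it through.** **No plan figure to reproduce.** The documents state no agreement, kappa or precision for this objective. The only number in the Analysis plan is the recruitment target in "we will calculate the time to recruit 1500 participants and the cost per study completer", which is a feasibility target. Everything below is illustration on assumed inputs.

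**Step 1: shift in the confirmation rate.** Let u be the share of reported diagnoses whose record is unclear, g the proportion of these confirmed when the claim is known, and t the proportion confirmed by masked reading. The confirmation rate among reported diagnoses shifts by u × (g − t).

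- Low end: 0.05 × 0.20 = 0.01, or 1 point.
- High end: 0.30 × 0.40 = 0.12, or 12 points.

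**Step 2: shift in whole-cohort agreement.** If agreement is computed disease by disease over all participants, only those who reported the disease contribute the shift, so it is multiplied by the self-report prevalence s.

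- s = 10%: 0.10 × 1 = 0.1 points to 0.10 × 12 = 1.2 points.
- s = 40%: 0.40 × 1 = 0.4 points to 0.40 × 12 = 4.8 points.

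**Step 3: effect on kappa.** Further assumptions: 85% of clear records confirm the report, 3% of people not reporting the disease are reference-positive (so they too have a reference result), and t = 50%. The confirmation rate is (1 − u) × 0.85 + u × g. At u = 10%:

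- masked, g = 50%: 0.765 + 0.050 = 81.5%
- always siding with the claim, g = 100%: 0.765 + 0.100 = 86.5%
- strict, g = 25%: 0.765 + 0.025 = 79.0%

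Kappa is (po − pe)/(1 − pe). For s = 10%, masked: po = 0.0815 + 0.873 = 0.9545; pe = 0.10 × 0.1085 + 0.90 × 0.8915 = 0.8132; kappa = 0.1413/0.1868 = 0.756. The other cells follow in the same way.

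| Unclear share u | Confirmation rate, masked → always siding with claim | Kappa, s = 10% | Kappa, s = 40% |
|---|---|---|---|
| 5% | 83.3% → 85.8% | 0.768 → 0.783 | 0.819 → 0.841 |
| 10% | 81.5% → 86.5% | 0.756 → 0.788 | 0.804 → 0.848 |
| 20% | 78.0% → 88.0% | 0.734 → 0.797 | 0.773 → 0.861 |

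The right-hand value in each pair is the extreme case in which every unclear record is resolved for the participant.

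**Step 4: the opposite direction.** With strict adjudication (g = 25%) at u = 10%, kappa falls from 0.756 to 0.740 (s = 10%) or from 0.804 to 0.781 (s = 40%). The sign depends on how adjudicators behave.

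**Step 5: comparison with sampling error.** If 85% of 1500 reported diagnoses were confirmed, the 95% half-width would be 1.96 × √(0.85 × 0.15/1500) = 0.018, or 1.8 points. A shift at the upper end of Step 1 would exceed this, and one at the lower end would not. Single-disease counts will be smaller and their intervals wider.

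**The case against.** The strongest reply is that the article never says adjudicators see the self-report or count it as evidence. The sentence about uploads uses the same adjective for the diagnosis shown in the record, so the adjudication rule can be read as interpreting an unclear document and nothing more. Masking and adjudication criteria are operating details that a condensed article commonly leaves to a full protocol or manual. The test of whether a diagnosis can be confirmed also lets a vague record fail, so agreement could go down. The physician form and the requirement that the upload show the diagnosis should keep unclear records few. Finally, the inputs behind any magnitude are assumed.

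Much of this stands. A reader might infer that the whole reference standard depends on the self-report and that agreement is definitely biased upward; the documents support neither. Use of the claim in adjudication is an inference from the wording. The direction is likely but not certain. The problem is confined to unclear records, since clear entries and clear physician forms come from outside the study. The absence of a masking statement would not by itself be a finding.

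What does not fall is the framing. The article fixes the adjudication question, and in a section about verifying self-reports that question most naturally means confirming what the participant reported. An unpublished masking step would reduce the risk, but the wording would still need correcting: an adjudicator who does not know the claim can classify a record but cannot confirm the claim.

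**Conclusion.** The concern holds in a limited form. For unclear records, the reference used for percent agreement and kappa may not be independent of the self-report, and agreement may be inflated. The 1 to 12 point range is a shift in the confirmation rate among reported diagnoses and rests wholly on the assumed 5-30% unclear and 20-40 points of extra confirmation. It should not be read as a shift in whole-cohort agreement, which is smaller in proportion to self-report prevalence. On the separate kappa assumptions, the rise is about 0.015 to 0.09 when 5-20% of records are unclear and adjudicators always side with the claim. The lower end is of little consequence; the upper end would matter for a validity claim. In either direction, the result for these records would partly reflect adjudicator leniency. This is worth correcting because validation is a stated aim and the remedy is cheap, but it does not invalidate the objective.

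**What to change.** Reword the adjudication rule in Diagnosis Verification. The adjudicators already planned read each unclear record without the self-reported diagnosis and record which of the listed diseases it documents (OA, gout, fibromyalgia, RA, PsA, lupus, other; more than one allowed), with an undetermined result permitted. The comparison with self-report is made only afterwards.

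In the Analysis plan, report percent agreement and kappa twice, once with undetermined records counted as not confirmed and once with them excluded, and state how many records were unclear. That count supplies the figure now missing for judging the size of the problem.

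The cost is a REDCap view that hides the self-report field, plus an extra table row. No new data or participant contact is needed. The downside is that reported agreement may be slightly lower. The change is best made before adjudication starts, because records already judged with the claim in view would have to be read again.
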